### Patient and public involvement

Prior to trial implementation, a CAG (n=16) of mothers from Soweto with infants aged 0–3 months will be established to serve as experts on the lived experience of being a mother to an infant in Soweto. For about half of these women, family matriarchs will be recruited to form a separate CAG (n=8). Research from South Africa has indicated that family matriarchs play an important role in the choices that mothers make around infant feeding and nutrition,^13^ and as such it is pertinent they be included in interventions targeting breast feeding and other child care practices.

Intervention content and activities, and behavioural feedback will be tested and/or developed with the CAG, using FGDs and piloting of intervention content and feedback. Thus, the initial acceptability and feasibility of the intervention content will be tested by the CAG in order to understand any changes required, and thus refine the intervention accordingly.

The CAG will continue to advise throughout the duration of the intervention, via regular (every 4 months) FGDs where the research team will raise queries about intervention content, delivery and uptake, retention strategies, and feedback mechanisms. Additionally, the CAG will provide important insight into their lived experience of being a mother in Soweto over time and as their infant grows. This will provide useful insight to guide intervention conversations and to better understand the context within which the intervention is being delivered.

### Monitoring

Monitoring of intervention activities will be done throughout the trial. The delivery of each contact (duration, date, content) will be recorded using a monitoring log in order to be able to monitor intervention intensity and frequency. Engagement with the app content and behavioural feedback (ie, number of page visits per day and duration of time spent on the app) will be monitored via the app.

Adherence will be assessed every 4 months, and strategies to improve adherence will be discussed with the CAG as necessary. Additionally, the research team will meet with HHs weekly to determine any concerns or issues with compliance or retention, and strategies will be discussed accordingly. Any adverse events will be recorded and reported as necessary according to standard operating procedures.

### Sample size

Given expected attrition of 30%, recruiting 210 mother–infant pairs should yield a final sample size of 150 mother–infant pairs, which will be divided into 2 groups (n=75 each). A sample size of 150 mother–infant pairs divided into 2 groups (n=75 each; control and trial group) will allow for 99% power to detect efficacy of the intervention based on maternal self-efficacy data assessed in the piloting phase of the behavioural feedback intervention (data not yet published).

Attrition will be minimised by maintaining regular contact with both groups, by recruiting participants who plan on remaining in Soweto, and by using a flexible and versatile delivery approach including in-person visits, app-based content, telephonic sessions, mobile messaging and site visits.

### Data analysis plan

The efficacy of the intervention will be assessed using intention to treat analysis. Secondary outcome data will be compared between the intervention and standard of care arms using Student’s unpaired t-tests. Focus will be placed on the primary efficacy outcome (maternal self-efficacy) due to limited power for secondary outcomes, which will therefore be treated with caution and presented using point estimates and precision (95% CI). Sensitivity analyses will include comparing baseline characteristics between intervention and standard of care arms, examining the effect of intervention dose on outcome data and stratifying analyses by sex.

The feasibility and acceptability of the intervention at each phase will be assessed using qualitative and quantitative methods. FGDs will be transcribed and coded line by line, and data will be grouped according to common themes. Themes will be sorted into subthemes and continually reviewed to identify an overarching narrative to identify key findings from each FGD.

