#### Secondary outcomes at 12 months

Infant development at 12 months compared between the intervention and control groups using the Ages and Stages Questionnaire (ASQ3).Feasibility and acceptability of the health literacy and behavioural feedback intervention.Change in infant weight to length ratio compared between intervention and control groups.Infant fat mass index (FMI) (assessed using dual X-ray absorptiometry (DXA) fat mass divided by length) compared between intervention and control groups.Change in maternal health literacy from 6 to 12 months compared between intervention and control groups.Change in maternal mental health from 0 to 12 months compared between the intervention and control groups.Infant movement behaviours compared between intervention and control groups.Mother–infant interaction styles compared between intervention and control groups.

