Compliance will be assessed by counts (eg, login frequency on app, delivery of messages and monitoring of phone calls using a log) and by discussions with the HHs.Intervention dose will be monitored by recording the frequency and duration of contact as well as the topics of conversation between participants and HHs or feedback given to participants using the logs.To understand the mechanisms through which the intervention brings about change in specified outcomes, women’s experiences of receiving the intervention, contact with HHs and the app will be assessed using questionnaires and focus groups at the close of each intervention phase. We will also use the secondary outcomes (process data) to determine whether individual proposed pathways of impact are effective prior to analysing trial outcomes.In considering the context, identification of factors that might act as barriers or facilitators to intervention implementation or effects will be assessed. This will include local and national policy, local service configuration and provision, and sociodemographic and environmental factors of the participants. Our approach to assessing context will be through a combination of policy mapping, quantitative data collection and longitudinal consultation with the CAG.

Maternal breastfeeding self-efficacy will be assessed every 2 months from 0 to 6 months using the Breastfeeding Self-Efficacy Short Form.^58^ This comprises 14 questions, each with a 5-point Likert response scale ranging from 1=not at all confident to 5=very confident. The higher the final aggregate score (which has a range of 14–70), the higher the level of breastfeeding self-efficacy.

Exclusive breast feeding will be assessed every 2 months from 0 to 6 months by asking mothers whether they are currently breast feeding and if not, at what infant age did they stop breast feeding and why they stopped breast feeding. They will also be asked if they are giving their infant anything other than breastmilk, and if so, why.

Weight and length will be measured by trained research staff at baseline and 12 months (and at 4 and 8 months). Weight-to-length ratio (kg/m) will then be calculated to estimate anthropometric changes in body composition. At 12 months, DXA scans will be performed by a trained technician. Whole-body measurements of fat mass and fat-free mass will be extracted for use in analyses. FMI (kg/m^3^) will be calculated from these estimates to describe adiposity.

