Health literacy will be assessed at 6 and 12 months using the parent version of the Health Literacy Questionnaire,^59^ which covers nine areas of health literacy including functional health literacy and has been validated in high-income and low-to-middle-income countries.

Various aspects of maternal mental health will be assessed at baseline, 4 and 12 months. The PCL-5^60^ will be administered whereby rating scale descriptors include: ‘not at all’, ‘a little bit’, ‘moderately’, ‘quite a bit’ and ‘extremely’. A total symptom severity score is calculated by adding up the item scores, which range from 0 to 80. The cut-off for PTSD that will be used in this study was 31. The EPDS^61^ will be used to detect postnatal depression. Scores for each item range from 0 to 3 on a Likert scale and are added together to obtain an overall total. Scores of 7–13 indicate mild depression, 14–18 moderate and 19–30 severe depression. The ACE Questionnaire^62^ will assess childhood abuse, neglect and household challenges. A score from 0 to 10 is calculated based on how many types of events were experienced before 18 years old. The ASQ will be administered to assess stressful life events. An additional nine items about social support will be included. The Postpartum Bonding Questionnaire^63^ will be used to detect early mother–infant bonding. It consists of four subscales ‘impaired mother/infant bonding’, ‘rejection and anger’, ‘anxiety about care’ and the ‘risk of abuse’. These questions are rated on a 6-point Likert scale, ranging from 0 (always) to 5 (never).

Infant adherence to movement guidelines will be assessed every 4 months using accelerometery. Seven-day, 24-hour wrist worn accelerometery data (Axivity-AX3 worn on both mother and infant) will be collected, downloaded (omgui, Open Movement, UK), auto-calibrated and processed. Data is summarised to generate average acceleration (mg) per 5 s interval, as well as overall time (hourly and weekly) spent in varying intensities of activity, which will allow for determination of adherence to movement guidelines and changes in activity levels over the intervention period.

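### Weight-to-length ratio and maternal mental health are to be compared by unadjusted t-tests on change scores, although adjusting for the pre-randomisation baseline would generally give narrower confidence intervals

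*Protocol article*

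**What the plan says.** The Data analysis plan fixes one method for all secondary outcomes: "Secondary outcome data will be compared between the intervention and standard of care arms using Student’s unpaired t-tests". It explains that emphasis falls on the primary outcome "due to limited power for secondary outcomes, which will therefore be treated with caution", and that results will be "presented using point estimates and precision (95% CI". No covariate is named. The only role given to baseline data there is a check of how the arms compare at baseline, filed under sensitivity analyses.

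Under Secondary outcomes at 12 months, two outcomes are changes from baseline: "Change in infant weight to length ratio compared between intervention and control groups" and "Change in maternal mental health from 0 to 12 months compared between the intervention and control groups". Both have a starting value. For growth, "Weight and length will be measured by trained research staff at baseline and 12 months (and at 4 and 8 months". For mental health, "Various aspects of maternal mental health will be assessed at baseline, 4 and 12 months". The Study design section has the allocation generated only once recruitment and baseline assessment are finished, so these values precede randomisation.

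A third outcome is less clear: "Maternal breastfeeding self-efficacy will be assessed every 2 months from 0 to 6 months using the Breastfeeding Self-Efficacy Short Form". It is not worded as a change, and its first score is not called a baseline.

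**The concern.** A baseline measured before randomisation is a legitimate covariate and usually predicts the follow-up value. An unpaired t-test on the change uses that baseline only by subtracting it in full. Regressing the follow-up value on arm and baseline (ANCOVA) estimates how much to subtract, and in large samples cannot do worse.

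At stake is the width of the intervals. The plan itself says power for these outcomes is limited and makes the point estimate with its 95% CI the basis for reading them. An analysis that widens those intervals without need works against that aim, when the data to narrow them are already being collected.

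**Working it through.** **Plan's own figure.** No power or precision figure is given for any secondary outcome, so there is nothing to reproduce. The 99% power under Sample size concerns maternal self-efficacy only.

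**Inputs from the protocol article.** 75 pairs per arm after attrition (Sample size); unpaired t-tests and 95% CIs (Data analysis plan); weight and length at baseline, 4, 8 and 12 months; mental health at baseline, 4 and 12 months.

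**Assumed inputs, because the documents give none.** ρ, the correlation of baseline with 12-month value, at 0.3, 0.5 and 0.7; k, the baseline SD divided by the 12-month SD, at 0.5, 0.7 and 1.

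**Formulas.** Per-arm variance, with the 12-month variance set to 1:
- follow-up value alone: 1
- change score: 1 + k² − 2ρk, which is 2(1 − ρ) when k = 1
- baseline-adjusted: 1 − ρ²

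The change-score variance minus the adjusted variance is k² − 2ρk + ρ² = (k − ρ)². This is never negative and is zero only when k = ρ.

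**Equal SDs (k = 1).** The variance ratio, change to adjusted, is 2(1 − ρ)/(1 − ρ²) = 2/(1 + ρ), giving 1.54, 1.33 and 1.18. The square roots give the CI width ratios: 1.2403, 1.1547 and 1.0847. With 75 per arm the CI half-width is 1.976 × √(2/75) × s = 0.323 × s, where s is the square root of the relevant variance:

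| ρ | Follow-up only | Change score | Adjusted | Change CI wider by | Follow-up-only CI wider by |
|---|---|---|---|---|---|
| 0.3 | 0.323 | 0.382 | 0.308 | 24% | 5% |
| 0.5 | 0.323 | 0.323 | 0.279 | 15% | 15% |
| 0.7 | 0.323 | 0.250 | 0.230 | 8% | 40% |

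Simulating 1,000 trials of this size at each correlation gave mean half-widths of 0.380 and 0.308, 0.322 and 0.280, and 0.249 and 0.230 for change and adjusted analyses, in agreement.

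As an illustration, take a true difference of 0.4 SD (assumed). At ρ = 0.5, power is 69% for the change-score test and 81% with adjustment. At ρ = 0.3 it is 54% and 73%.

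**Smaller baseline SD.** Newborns may vary less in weight-to-length than 12-month-olds, so k may be below 1. For k = 0.7 and ρ = 0.3: change 1 + 0.49 − 0.42 = 1.07; adjusted 1 − 0.09 = 0.91; width ratio √(1.07/0.91) = 1.084. In full:

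| k | ρ = 0.3 | ρ = 0.5 | ρ = 0.7 |
|---|---|---|---|
| 0.5 | 1.022 | 1.000 | 1.038 |
| 0.7 | 1.084 | 1.026 | 1.000 |

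So for k of 0.5 to 0.7 the loss is about 0 to 8%.

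**When a change score does worse than ignoring the baseline.** This needs 1 + k² − 2ρk > 1, that is ρ < k/2. The threshold is 0.5 at k = 1, 0.35 at k = 0.7 and 0.25 at k = 0.5.

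**The case against.** The strongest reply is that nothing here is invalid. These are secondary outcomes, the plan already promises caution, and a condensed article may leave covariates to an analysis plan that is not shown. The first two points stand and keep the matter small. The third stands only in part: the article does not leave the method open but names the unadjusted t-test for all secondary outcomes.

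Four stronger readings are tempting and should be resisted.

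- *The baseline values are thrown away.* A change score uses the baseline, with its slope fixed at 1. The two outcomes with a clear baseline are both change scores. The description could fit breastfeeding self-efficacy only if a month-0 score precedes randomisation and later scores alone are compared. The document states neither, and it also places the newborn behavioural assessment, an intervention component, at recruitment.
- *Chance imbalance under simple randomisation biases the result.* With 75 per arm the baseline difference has standard error √(2/75) = 0.16 SD, so gaps up to about 1.96 × 0.16 = 0.32 SD are ordinary. At ρ = 0.5 and equal SDs, such a gap moves a change-score estimate by (1 − 0.5) × 0.32 = 0.16 SD. Over repeated randomisations the estimate is still unbiased, and the CI already allows for this variation. The loss is one of precision.
- *Intervals will be about a quarter too wide.* That needs both ρ = 0.3 and equal SDs. For weight-to-length the loss may be close to nil.
- *All secondary outcomes are affected.* Infant development on the ASQ3 and fat mass index have no baseline, and none is stated for movement or interaction measures. The change in health literacy starts at 6 months, after randomisation. The primary outcome is untouched: self-efficacy is assessed at 6 and 12 months only.

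**Conclusion.** The point holds in a limited form. The plan fixes a valid but generally less efficient analysis for weight-to-length ratio and maternal mental health, the two outcomes whose baseline clearly precedes randomisation. With equal SDs, CIs are about 24%, 15% and 8% wider than necessary at ρ of 0.3, 0.5 and 0.7. With a baseline SD of 0.5 to 0.7 of the 12-month SD, the excess is about 0 to 8%. The larger figures suit EPDS and PCL-5 better, if their spread stays similar over the year. All of these rest on assumed correlations and SD ratios. The formulas, and the fact that adjustment does not materially lose precision, do not depend on those values. Breastfeeding self-efficacy belongs here only conditionally. The change is worth making because it costs almost nothing, not because the planned tests mislead.

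**What to change.** In the Data analysis plan, limit the t-test to continuous secondary outcomes without a pre-randomisation value, and add:

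- For weight-to-length ratio, EPDS and PCL-5, compare the 12-month value between arms by linear regression adjusted for the same measure at baseline. Alternatively, use a baseline-adjusted mixed model that includes the intermediate visits (4 and 8 months for growth, 4 months for mental health). Report the adjusted difference with its 95% CI.
- State whether the month-0 breastfeeding self-efficacy score is taken before randomisation. If so, analyse the later scores in the same way.
- Name the instruments that make up the mental health outcome, and do not analyse the ACE score as a change. It counts types of event before age 18, and eligible mothers are at least 18, so it cannot truly change.

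The cost is a few sentences of analysis wording, best settled before any comparison of outcomes by arm. No new data, visits or participants are needed.

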### Integrating nutrition into caregiving interventions

In the first 6 months of an infant’s life, exclusive breast feeding is regarded as the optimal and most nutritionally complete form of infant nutrition.^7 8^ Research indicates that infants who are breast fed for longer may have higher cognitive function, and lower infectious morbidity and mortality. Breast feeding may also protect against diabetes, cardiometabolic disease and overweight later in life.^7^ It is estimated that improving global breastfeeding rates alone could potentially prevent more than 800 000 children deaths annually.^7^ Despite the widely established benefits of breast feeding, in the South African context, roughly 67% of infants initiated breast feeding within the first hour of birth in 2016, yet only 32% of children under the age of 6 months remain exclusively breast fed. The mean duration of exclusive breast feeding was found to be only 2.9 months,^9^ with widespread introduction of solid foods and non-breastmilk liquids before 3 months.^10 11^ Breastfeeding self-efficacy has been found to directly influence breastfeeding practices, and high breastfeeding self-efficacy was found to play a critical role in exclusive breastfeeding duration in the South African setting.^12^

Qualitative findings from urban South Africa reported that infant nutrition interventions in this context should focus on: fostering maternal self-efficacy around exclusive breast-feeding; challenging mixed feeding practices and encouraging more responsive feeding approaches; and engaging family members to promote supportive household and community structures around infant feeding.^13^

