#### Secondary outcomes at 6 months

Breastfeeding self-efficacy from 0 to 6 months compared between intervention and control groups.Exclusive breast feeding from 0 to 6 months compared between intervention and control groups.Feasibility and acceptability of the breastfeeding intervention.

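### Student's t-test is fixed for every between-arm secondary outcome, including exclusive breastfeeding from 0 to 6 months, and the feeding questions as described do not give the age at which exclusivity ended

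*Protocol article*

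**What the plan says.** The protocol article's Data analysis plan names one test: "Secondary outcome data will be compared between the intervention and standard of care arms using Student’s unpaired t-tests". It adds that secondary outcomes have limited power and will be reported cautiously, as point estimates with 95% confidence intervals. Only feasibility and acceptability get a method of their own: "The feasibility and acceptability of the intervention at each phase will be assessed using qualitative and quantitative methods".

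The list of secondary outcomes at 6 months includes: "Exclusive breast feeding from 0 to 6 months compared between intervention and control groups". Under Hypotheses, better breastfeeding exclusivity is the result expected from the breastfeeding support.

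Under Secondary outcome measures, mothers are asked every 2 months "whether they are currently breast feeding and if not, at what infant age did they stop breast feeding and why they stopped breast feeding". The text continues: "They will also be asked if they are giving their infant anything other than breastmilk, and if so, why". It does not say how these answers become one outcome covering 0 to 6 months.

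**The concern.** An unpaired t-test needs one number per mother. Here each mother supplies several yes/no answers over 6 months, and an age only if she has stopped breastfeeding altogether. To apply the stated test, someone must choose between one visit's status and some form of duration, and the article does not say which.

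The data raise a second difficulty. Exclusivity can end while breastfeeding continues, because the infant starts to receive other foods or liquids as well. The age at stopping breastfeeding does not capture that event. The Introduction describes mixed feeding as the local pattern, with other foods and liquids widely introduced before 3 months, so in many infants exclusivity may end in this way.

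At stake is how much can be learned about the second hypothesis. An analysis plan written later can change the test, but it cannot recover an age that was never asked.

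**Working it through.** **1. What the questions can and cannot give**

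| Needed for exclusivity from 0 to 6 months | Asked, as described? |
|---|---|
| Exclusive at each contact | Yes: current breastfeeding and current other feeds |
| Age when any breastfeeding stopped | Yes, if it has stopped |
| Age when other feeds were first given | No: current use and reason only |
| Other feeds given and stopped between contacts | No question about the interval |

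With these answers, the end of exclusivity is known only to lie between the last exclusive and the first non-exclusive contact, about 2 months apart. A feed begun and stopped between contacts is missed. The documents give no frequency for that.

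**2. Is the t-test invalid for one yes/no status?** No. The Introduction gives an illustrative rate: "only 32% of children under the age of 6 months remain exclusively breast fed". Exact binomial enumeration with 75 per arm gives, at a common rate of 32%, a type I error of 4.85% for both the t-test and the pooled chi-square test. For 32% against 52%, power is 71.9% and 72.2%.

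**3. What is the timing information worth?** The article gives no power figure for this outcome, so this is an illustration.

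Inputs:
- Mean exclusive duration 2.9 months (Introduction).
- 210 × 0.70 = 147 retained (Sample size), so about 74 per arm.
- Assumed: exponential durations, hazard ratios (HR) 0.67 and 0.60, two-sided 5%, exact ages, no dropout before 6 months.

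Proportion still exclusive at 6 months, S(6) = exp(−6·HR/2.9):
- Control: 0.126.
- HR 0.67: 0.250. HR 0.60: 0.289.

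Snapshot at 6 months, power = Φ(|p1 − p0| / √{[p0(1 − p0) + p1(1 − p1)]/74} − 1.96):
- HR 0.67: 0.1237/0.0634 = 1.95, power 49.6%.
- HR 0.60: 0.1627/0.0653 = 2.49, power 70.2%.

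T-test on ages cut at 6 months. With λ the hazard in each arm, the mean is (1 − e^(−6λ))/λ and the mean square is (2/λ²)[1 − e^(−6λ)(1 + 6λ)]. The control mean is 2.53 months (SD 1.97).
- HR 0.67: mean 3.25 (SD 2.14); 0.712/√[(1.97² + 2.14²)/74] = 2.11, power 56%.
- HR 0.60: mean 3.44 (SD 2.16); 0.903/√[(1.97² + 2.16²)/74] = 2.66, power 76%.

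Log-rank test, power = Φ(½√d·|ln HR| − 1.96), with d the number of events:
- HR 0.67: d = 74 × (0.874 + 0.750) = 120; 2.19 − 1.96, power 59%.
- HR 0.60: d = 74 × (0.874 + 0.711) = 117; 2.77 − 1.96, power 79%.

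Simulation of the same settings gives 50%/70%, 56%/75% and 60%/79%, in agreement to about one point.

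**4. Reading the gaps.** Snapshot to log-rank is about 9 to 10 points. Most of that comes from discarding timing. The t-test on cut ages gives up only about 4 points to the log-rank test. Both of these need the age at end of exclusivity, which the questions as described do not collect.

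**The case against.** The strongest defence is that the outcome is secondary, is declared to have limited power and will be reported cautiously with confidence intervals, while the primary outcome is untouched. Also, ages cut at 6 months give a well-defined restricted mean over the window that the outcome names, and a t-test on it loses little. Both points stand, and they limit the consequence. They do not remove the point, because the restricted mean needs the missing age and the article does not say that it is intended.

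It can also be said that the article paraphrases a questionnaire that is not shown. That is fair: if the form already asks the age at first introduction, only the text needs correcting. The test and the questions are, however, stated in the article, so this is not mere detail left to an unseen plan.

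A reader might infer more than the documents support:
- **Feasibility and acceptability would be t-tested.** They have their own method in the next paragraph of the Data analysis plan.
- **The movement outcome is equally unsuited.** It is summarised mainly as average acceleration and time in intensities, which are continuous. The data are also described as something "which will allow for determination of adherence to movement guidelines", but yes/no scoring is not stated.
- **Exclusivity is materially overstated.** Missed feeds would push that way, but no rate of return to breastmilk alone is given.
- **30% of durations are censored by dropout.** That is the expected attrition for the final sample; no 6-month figure is given.
- **The t-test costs about 9 points of power, or far more.** The larger gap is snapshot against log-rank. Very low power (18% against 66% for log-rank at HR 0.65, 75 per arm) arises only if mothers still breastfeeding at 6 months are dropped, which the article does not propose.

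**Conclusion.** The point holds in a limited form. One test is fixed for all between-arm secondary outcomes, and it does not suit exclusive breastfeeding from 0 to 6 months as collected. The questions as described give status at each contact but neither continuous exclusivity nor the age at which it ended. The loss is of information, not of type I error control.

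The size is moderate: roughly 9 to 10 points of power between a 6-month snapshot and a time-to-event analysis, of which only about 4 are due to using a t-test on cut ages rather than a log-rank test. These figures rest on assumed exponential durations, hazard ratios and a two-sided 5% level, with exact ages and no early dropout. The exponential shape is rough: it implies an average exclusive rate under 6 months of 2.53/6 = 42% if ages are evenly spread, against the 32% cited. The absence of the age question does not depend on any of these assumptions. The change is worth making because the outcome carries the second hypothesis and the gap is hard to repair after data collection.

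**What to change.** 1. In the Data analysis plan, limit t-tests to continuous secondary outcomes.
2. At each 2-monthly contact to 6 months, also ask whether anything other than breastmilk has been given since birth or the last contact, and the infant's age when it was first given.
3. Define the outcome as age at end of exclusivity, censored at 6 months or last contact. Analyse it by Kaplan-Meier with a log-rank test or Cox model, or by an interval-censored method where the end is known only to a window between contacts.
4. Report the proportion exclusive throughout to 6 months as a risk difference with 95% CI.
5. If adherence to movement guidelines is reported as yes/no, give it as a risk difference too.

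The cost is one added question in an existing interview and a few lines of analysis text. The downside is slight recall error in the reported age, which the 2-month recall period should keep small. If data collection has begun, mothers not asked from the start can still contribute through the interval-censored analysis of their recorded statuses, with feeds between contacts unseen.

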### Study design

The PLAY Study was designed following the Standard Protocol Items: Recommendations for Interventional Trials 2013 statement.^49^ Mother–infant pairs (n=210) will be recruited starting in the third quarter of 2022 until the second quarter of 2023, and individually randomised into two groups (total n after expected attrition=150, n=75 in each group) using simple 1:1 randomisation generated by Stata V.17. The intervention will last from birth to 12 months, with main assessments made when the infants are 0, 6 and 12 months of age. The trial will consist of a standard of care arm and an intervention arm—see figure 1. Data collection teams will be blinded to randomisation at baseline and during primary outcome assessments, and separate data collection teams will collect baseline compared with primary outcome data. Blinding will be maintained by the data manager and broken only for a priori defined analyses (figure 2). Randomisation into either group will be generated by the data manager only after recruitment and baseline assessments are completed, whereafter participants will be assigned to the intervention delivery teams accordingly (intervention delivery teams will thus not be blinded). Intervention delivery teams will work separately and independently of each other, and of data collection teams. The trial is due to be completed in the second quarter of 2024.

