#### Primary outcome at 12 months

Maternal self-efficacy at 12 months compared between intervention and control groups.

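### The dose and sex analyses listed as sensitivity analyses do not test the intention-to-treat result, and as worded they invite unsupported dose-response and one-sex claims

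*Protocol article*

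**What the plan says.** The article's Data analysis plan gives the main approach in one sentence: "The efficacy of the intervention will be assessed using intention to treat analysis". The primary outcome section defines the comparison as "Maternal self-efficacy at 12 months compared between intervention and control groups". The plan then lists sensitivity analyses. One item is a baseline comparison between arms. The other two are "examining the effect of intervention dose on outcome data and stratifying analyses by sex".

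Dose is defined under Secondary outcome measures, in the process evaluation: "Intervention dose will be monitored by recording the frequency and duration of contact", together with the topics discussed and the feedback given. App logins appear in the same section, but under compliance rather than dose.

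The intervention sections show what drives dose. Themed contacts are scheduled every 2 months and behavioural feedback every 4 months. Mothers steer the conversation, referrals follow need, and mothers who screen as high risk get a call, counselling and continuing support.

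On size, the Sample size section states: "Given expected attrition of 30%, recruiting 210 mother–infant pairs should yield a final sample size of 150 mother–infant pairs". That final sample "will allow for 99% power to detect efficacy of the intervention based on maternal self-efficacy data assessed in the piloting phase". Allocation is made "using simple 1:1 randomisation generated by Stata V.17", and no stratification by infant sex is mentioned.

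**The concern.** A sensitivity analysis asks whether the primary estimate survives a change in an assumption behind it. These two analyses ask other questions.

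- **Dose.** Relating dose to outcome compares mothers who took up more of the intervention, or needed more, with those who did not. Randomisation does not protect that comparison. Engaged mothers may already be more confident, which would produce a positive association. Struggling mothers may receive more contact, which would produce a negative one. The plan nonetheless calls the result an effect.
- **Sex.** Read in its usual sense, stratifying by sex means a separate treatment comparison in boys and in girls. Each has half the sample. A significant result in one and not the other is easily read as a difference between the sexes, although no difference has been estimated.

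The article's Discussion looks ahead to wider implementation if the intervention succeeds. A spurious statement that more contact works better, or that the intervention works in one sex only, could shape what is scaled up. The intention-to-treat comparison would not change. What is at stake is the supporting interpretation.

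**Working it through.** **Inputs from the article:** 210 recruited, 30% attrition, 150 remaining, 75 per arm, 99% power.

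**Assumptions, because the article does not give them:** two-sided alpha of 0.05, equal numbers of boys and girls, and the correlations in step 3.

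**1. The plan's own figures.** Retention: 210 × (1 − 0.30) = 147, close to the stated 150 (exact loss 60/210 = 28.6%). I use 147/2 ≈ 74 per arm and 74/2 = 37 per arm per sex; using 75 makes no material difference. The 99% power cannot be reproduced, because no effect size or SD is stated. The implied standardised effect is

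d = (1.960 + 2.326) × √(2/75) = 4.286 × 0.1633 = 0.70.

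**2. Separate analyses by sex, same true effect in both.** Let p be the power of a two-sided unpaired t-test with 37 per arm. The two sexes are independent, so P(exactly one significant) = 2p(1 − p).

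| True d in each sex | p | P(exactly one significant) |
|---|---|---|
| 0.70 (implied by 99% power) | 0.844 | 2 × 0.844 × 0.156 = 0.26 |
| 0.50 (illustrative) | 0.564 | 2 × 0.564 × 0.436 = 0.49 |

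For the interaction (the difference between the sex-specific effects), SE = √(4/37) = 0.33 SD. Its 95% CI extends 1.96 × 0.33 ≈ 0.64 SD either side. Power is about 57% for a true difference of 0.70 SD and 33% for 0.50 SD. The difference detectable with 80% power is (1.96 + 0.84) × 0.33 ≈ 0.92 SD.

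**3. Dose within the intervention arm, no true effect of dose.** Suppose an unmeasured engagement factor correlates ρ with dose and ρ with 12-month self-efficacy. The induced dose–outcome correlation is r = ρ². By Fisher's transformation with n = 74, P(significant and positive) ≈ P(Z > 1.96 − atanh(r) × √71).

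| ρ (assumed) | r | atanh(r) × √71 | P(significant, positive) |
|---|---|---|---|
| 0.2 | 0.04 | 0.34 | 5% |
| 0.3 | 0.09 | 0.76 | 11.5% |
| 0.4 | 0.16 | 1.36 | 27% |

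The nominal rate is 2.5%. Simulation of the same model agrees (27% at ρ = 0.4). If need rather than motivation drives dose, so that one of the two correlations is negative, the same percentages apply to a significant negative association.

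**The case against.** **The article states no flawed model.** It does not say how dose will be modelled, and stratifying could mean a pooled analysis adjusted for sex. Dose monitoring belongs to a declared process evaluation, and contacts run to a schedule. All of this is fair. The schedule limits how far dose can vary, but uptake, call length, topics and referrals still vary with the mother. The wording commits to an effect of dose, and the usual sense of stratified analysis is separate analyses. If adjustment was intended, one sentence would settle it.

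**The sizes rest on assumed inputs.** This stands. At d = 0.70 the one-sex figure is about half that at d = 0.5, and the dose figure falls to about 5% when the correlations are 0.2. They show what can happen and do not predict this trial.

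**The interaction test is weak.** True, and it should be said in the report. Its wide interval shows that uncertainty, where two separate p-values hide it.

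**Stronger readings that the document does not support:**

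- A reader might infer that nothing will probe missing 12-month outcomes despite the 30% attrition. The list is introduced as open-ended, and such methods are commonly left to the analysis plan, so their absence here is no finding.
- A reader might take "Sensitivity analyses will include comparing baseline characteristics between intervention and standard of care arms" to mean significance testing of baseline differences. No test is mentioned, and a descriptive baseline comparison is normal reporting.
- A reader might count app logins, which mothers choose freely, as dose. The article files logins under compliance.

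**Conclusion.** The point holds for the dose and sex analyses. Neither is a sensitivity analysis of the intention-to-treat result: one is a confounded post-randomisation association and the other a subgroup analysis.

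Assuming two-sided 0.05 and a 50:50 sex split, separate analyses would give a significant result in exactly one sex in about 26% of trials at d = 0.70 and 49% at d = 0.5, with identical true effects. With no true effect, a positive dose association would be significant in about 5% to 27% of trials for assumed correlations of 0.2 to 0.4, against a nominal 2.5%. The direction of the dose bias cannot be known in advance.

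The document does not support a conclusion that the primary analysis is invalid; that comparison is untouched. The point matters for interpretation and is worth correcting before unblinding.

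**What to change.** Two changes to the Data analysis plan:

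1. Replace the sex-stratified tests with one treatment-by-infant-sex interaction estimate and its 95% CI. Report it as exploratory and state that its power is low.
2. Reword the dose analysis as a descriptive association within the intervention arm, and state that it supports no causal or dose-response claim.

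Neither should be called a sensitivity analysis.

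A complier-average effect defined by receipt of the 4- and 8-month feedback should not take the place of the dose analysis. Intervention mothers who miss that feedback still receive the newborn behavioural assessment, the app content and the themed contacts. Allocation can therefore affect their outcome by other routes, and the exclusion restriction fails.

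The cost is a few sentences and one extra model term. The plan gives up separate p-values by sex and the claim to a dose effect, neither of which this design can support well.
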